**Figure 3. f3:**
[figure not shown]
Study 3 design overview.

Study 3 has two additional aims related to improved characterisation of associations between RAR signals and short-term mood dynamics. The secondary aim of Study 3 is to examine the effect of baseline episode polarity—that is, whether the acute episode is depressive or manic—on the performance and structure of the predictive model. The analysis of Study 3’s secondary aim will investigate whether polarity moderates model accuracy against the binary outcome of 50% reduction in symptoms at 8 weeks, using 14 days’ actigraphy data. To increase the granularity of the investigation of this state transition, a tertiary aim of Study 3 is to explore temporal patterns in weekly RAR in relation to weekly clinician ratings of mood (MADRS, YMRS) and clinical state (CGI). The process-focus of this exploratory analysis takes advantage of the full 21 days of actigraphy.

Study 3 therefore investigates the prediction of acute treatment response from RAR variables amongst people who are experiencing a severe episode of BD [an important clinical question in its own right,
78]. Participants will be individuals with BD receiving guideline-based care and treatment
^
75
^ for acute manic (
*N* = 15) or bipolar depressive (
*N* = 30) episodes (on an inpatient, outpatient, or hybrid basis). Participants will be patients of Te Whatu Ora-Waitaha Canterbury Mental Health Services.

Three research questions address the development and testing of a state transition model, and its potential moderation by baseline episode polarity.
•Research Question 1: How many additional samples (
*x*) from the
*N* = 45 Study 3 sample are required to retrain the Study 1 complex system model predicting relapse (
*N* = 75) to achieve acceptable prediction accuracy for
*a state transition model* predicting both relapse amongst interepisode patients and response to treatment amongst acutely ill patients?•Research Question 2: Can a complex system model of state transition trained on
*N* = 75 Study 1 samples and
*x* (from Research Question 1) Study 3 samples predict state transition in an unseen data set of
*N* = 25 Study 1 samples and N = (45 –
*x*) samples from Study 3?•Research Question 3: Is episode polarity at baseline in the Study 3 cohort (
*n* = 30 depression versus
*n* = 15 manic) a moderator for the models developed in Research Question 1 and Research Question 2?

*Work Package 4: Integrative Data Synthesis*

Work Package 4 will develop an integrated relapse-risk algorithm that synthesises findings from the three preceding studies. The aim is to combine insights from statistical survival models, probabilistic network models, and non-linear dynamical models into a unified predictive framework. We will develop the integrated algorithm as a meta-model, using ensemble learning techniques to combine either the most informative features or the predicted probabilities from each of the component models. This approach will allow the algorithm to take advantage of the strengths of different analytical methods—statistical interpretability from survival models, multivariate pattern recognition from network models (and other forms of machine learning), and dynamic stability indicators from non-linear dynamic models. Model weighting, calibration, and validation will be performed using cross-validation and regularised optimisation to maximise generalisability and avoid overfitting. The resulting meta-model will provide individualised, probabilistic estimates of relapse risk, which can be iteratively refined as additional longitudinal data become available.

In addition to developing this ensemble meta-model, WP4 may include exploratory theoretical work aimed at integrating network-based and complex system approaches in the context of relapse prediction [see, e.g.,
79–
82]. Two lines of innovation are of particular interest. First, multi-perturbation Shapley-value analysis (MSA)
^
83
^ has been extended in our group to study temporal causal connectivity in brain and artificial neural networks.
^
84
^
^,^
^
85
^ MSA can be applied here to rank the relative contribution of variables (or network nodes) to relapse prediction for any given predictive or dynamical model. Second, the team has experience with excitable network modelling, which examines how small perturbations can propagate through a dynamic graph to reveal relationships between structural and functional connectivity.
^
86
^
^–^
^
88
^ These methods will be explored if data structure and model performance indicate potential for further mechanistic insight.

A detailed statistical analysis plan specifying the ensemble architecture, validation approach, and any additional exploratory analyses will be finalised and published prior to conducting analyses.

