The project involves four work packages. Three of these are prospective empirical studies amongst people living with BD. Study 1 (WP1, Australia) aims to predict early relapse by modelling RAR data. Study 2 (WP2, India) tests predictive models from RAR developed in Study 1 and tests the mechanistic relationship between a key RAR variable (Relative Amplitude, representing circadian robustness) and diurnal amplitude of gene expression and metabolites in blood. Study 3 (WP3, New Zealand) advances mechanistic understanding of the link between RARs and mood in BD by investigating a different state transition, namely, recovery from an acute episode, operationalised in response to evidence-based treatment. Thus, Studies 1 and 2 contribute to the project’s primary aim of algorithm development, and Studies 2 and 3 contribute (in different ways) to the secondary aim of improved mechanistic understanding of RAR variables in predicting BD course. Finally, WP4 is computational, conducting model comparison, cross-validation and synthesis using ensemble machine learning. A key output of WP4 is an open dataset and computational pipelines for sharing with future researchers.

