**Figure 2. f2:**
[figure not shown]
Study 2 design overview.

Three research questions and two hypotheses are therefore set for Study 2:
•Research Question 1: Does the Cox Survival Analysis model derived in Study 1 replicate amongst
*N* = 25 BD participants in an LMIC cohort?•Research Question 2: Does Dynamic Bayesian Network Analysis enable examination of relapse prediction amongst
*N* = 25 BD participants in an LMIC cohort?•Research Question 3: Does Hadaeghi’s Complex System Model of relapse prediction derived in Study 1 replicate amongst
*N* = 25 BD participants in an LMIC cohort?•Hypothesis 1: Amongst the complete sample (
*N* = 50), Relative Amplitude will correlate with the diurnal amplitude of both circadian gene expression and blood metabolites.•Hypothesis 2: Diurnal amplitude of circadian gene expression and blood metabolites, and Relative Amplitude will be attenuated in people with interepisode BD (
*N* = 25) compared to age, gender, and employment-matched healthy controls (
*N* = 25).

*Study 3: Exploring generalisability of the Complex System model of state transition from relapse prediction to treatment response.*

Study 3 contributes to the project’s secondary mechanistic aim by investigating if complex system features found in Study 1 to predict relapse (state transition into an episode) generalise to prediction of treatment response from an acute episode (state transition to recovery). If generalisation is demonstrated, it could be hypothesised that Hadaeghi’s Complex System Model captures generic system instability (as opposed to a relapse-specific process).

The primary aim of Study 3 is therefore to investigate whether the relapse risk algorithm informed by Hadaeghi’s Complex System Model (trained and tested on Study 1 data) can be extended to response to treatment.
^
19
^ The state transition of Study 3 is measured in binary response to treatment. Response to treatment at 8 weeks is operationalised as 50% reduction in MADRS (for those in depressive episode at baseline) or 50% reduction in YMRS (for those in manic episode at baseline). Participants will wear actigraphs for 21 days – for consistency with Study 1 and 2, the first 14 days only will be used in modelling of binary response to treatment.
Figure 3 below summarises the study design for this primary aim.

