*N* = 80 provides 83.8% power to detect a 65% increase in the relative risk of relapse. This suggests that even with a 20% dropout the study is nearly sufficiently powered to detect the expected relative risk of relapse (Hazard Ratio = 1.57) and powered to detect a slightly higher relative risk of relapse (Hazard Ratio = 1.65). Note also that the selected sample sizes of
*N* = 100 people with BD in Study 1, 50 in Study 2 (25 BD, 25 matched controls), and 45 in Study 3 (15 manic and 30 depressed) were pragmatic maxima. Recruitment beyond these pragmatic maxima will continue if resourcing permits.

*Cox Survival Analysis*

Cox Survival Analysis will be employed with Elastic Net
^
97
^ to determine variables to include. Relative Amplitude, Intradaily Variability, Interdaily Stability will be included as predictors in a random effects or frailty model of survival time to relapse (across the three epochs of Study 1 and the single epoch of Study 2). Initial time to first episode analysis: Proportional Hazards (Cox) regression with the five clinical covariates listed above. For the modelling of recurrent episodes a Prentice-Williams-Prentice (PWP) model will be used rather than a frailty model because the PWP is appropriate when only a small number of events is likely.
^
98
^

To model the relationship between the actigraphy signal and time to first episode, a two-stage joint survival model will be used. These models analyse time-to-event outcomes that may be linked to biomarkers that are repeatedly measured. A two-stage joint survival model analyses time-to-event outcomes influenced by a longitudinal, time-varying biomarker by fitting two separate models in sequence: a longitudinal model for the biomarker and a survival model for the event. This is a computationally efficient alternative to fully joint models, which can be very time-consuming to fit. The main drawback is that standard two-stage methods can disregard the uncertainty from the first stage’s estimates when they are used in the second, though advanced methods use techniques like multiple imputation to account for this.
^
99
^

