Survival analysis has shown that the probability of recovery is significantly lower from major depressive episodes compared to mania or hypomania. Recovery is also less likely from cycling episodes (switching between poles without a recovery period). This means that, ideally, manic and depressive episodes should be analysed together (suggesting a joint survival model for these two types of episode), but it is unclear if we will have sufficient data for this. Decisions will be made on review of the complete dataset and reported in the statistical analysis plan (forthcoming).

*Dynamic Bayesian Network Analysis*

Network analysis is a variant of machine learning designed to illuminate the architecture of complex systems.
^
97
^ In this project, network analysis is used to model potential causal pathways amongst sleep and circadian variables in the prediction of relapse. The analysis generates a graphical representation of nodes (individual characteristics and variables) and edges (connections and links among nodes). Location of nodes and strength/valence of links between nodes represent the specific association between two nodes while controlling for all other variables.

Scott and colleagues recently undertook a pilot study in a sample of young people with emerging BD and produced a network model of RAR variables relative to each other and to phenotypic features of BD.
^
33
^ This study found further support for the importance of robust circadian rhythmicity as measured in Relative Amplitude (see above). However, the authors highlight significant uncertainties in their modelling outcomes, concluding that “… whilst all research findings require replication and confirmation, we stress that this is particularly important in this emerging field of research” (p. 225).

The network analysis of Scott et al. was developed using cross-sectional data, while the present prospective project will permit exploration of how RAR variables change in relation to each other and to other BD symptoms over time. To model these temporal dependencies, Dynamic Bayesian Network Analysis will be applied. Dynamic Bayesian Networks are well suited to representing probabilistic relationships that evolve dynamically and can therefore capture time-dependent causal pathways among RAR, sleep, and clinical variables [see, e.g.,
100,

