The primary input data for all predictive modelling in Studies 1, 2 and 3 will consist of 14 days actigraphy time-series and derived features extracted through both time-domain and frequency-domain analyses. Feature extraction will include conventional RAR metrics such as the Van Someren variables (Relative Amplitude, Intradaily Variability, and Interdaily Stability), sleep–wake regularity, rhythm phase, and fragmentation, as well as signal-based features obtained from Fourier and wavelet analyses that capture periodicity, spectral power distribution, and nonstationary temporal patterns. Together, these actigraphy-derived metrics will form the principal set of predictors for analyses based on Cox Survival Analysis, Dynamic Bayesian Networks, Hadaeghi’s Complex System Model of BD and other machine learning approaches to be explored.

Auxiliary variables, including demographic and clinical data, will be used to support feature interpretation and to define model outcomes. In Studies 1 and 2, the primary outcome will be relapse, defined as the onset of a new depressive, manic or hypomanic episode meeting DSM-5 diagnostic criteria. Relapse will be identified through structured follow-up interviews using the LIFE (above). Time to first relapse will also be analysed as a survival outcome. In Study 3, the primary outcome will be treatment response, defined as at least a 50% reduction in baseline MADRS or YMRS scores at 8-week endpoint.

These outcome variables will be used to label actigraphy epochs and to train, validate, and compare predictive models of relapse risk and treatment response.

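### Study 3 tests whether polarity moderates model accuracy, a measure that can differ between depressed and manic patients only because their response rates differ

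*Protocol article*

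**What the plan says.** Section 2.2 of the Protocol article (Study 3, text after Figure 3) gives the secondary aim as the effect of baseline episode polarity "on the performance and structure of the predictive model". The next sentence says what will be done: the analysis "will investigate whether polarity moderates model accuracy against the binary outcome of 50% reduction in symptoms at 8 weeks". Research Question 1 also uses accuracy as its criterion; it asks how many Study 3 samples are needed "to achieve acceptable prediction accuracy for" a combined state-transition model. No formula, classification threshold or chance reference is given for accuracy.

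Section 2.6 defines the outcome as "at least a 50% reduction in baseline MADRS or YMRS scores at 8-week endpoint", using the depression scale or the mania scale according to the baseline episode. It gives the sample as "45 in Study 3 (15 manic and 30 depressed) were pragmatic maxima".

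Two further statements bear on the response rate. The Cox part of section 2.6 says that "the probability of recovery is significantly lower from major depressive episodes compared to mania or hypomania". Section 1.4 describes the Study 3 transition as "recovery from an acute episode, operationalised in response to evidence-based treatment".

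**The concern.** Percent correct mixes two things: how well the model separates responders from non-responders, and how many responders there are. When two groups have different response rates, their accuracies can differ although the model works equally well, or equally badly, in both.

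The moderation question asks whether rest-activity rhythms relate to recovery differently in depression and in mania. A gap in accuracy that comes only from the response rates would answer a different question. It would suggest that polarity changes how the model works when it may only change how often patients respond. The article's own statements on recovery make unequal rates a reasonable expectation.

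**Working it through.** The article gives no response rate, accuracy or power figure for Study 3, so there is nothing of its own to reproduce beyond 30 + 15 = 45. All response rates below are assumptions.

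**Formulas.** Let p be the response rate in a polarity group.
- Accuracy = sens × p + spec × (1 − p).
- If sensitivity and specificity are each the same in both groups, the accuracy gap (mania minus depression) = (sens − spec) × (p_mania − p_depression).
- A no-skill rule that predicts response with probability q, whatever the outcome, has sens = q and spec = 1 − q. Its gap is (2q − 1) × (p_mania − p_depression).

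**No-skill rule that always predicts response (q = 1), depression 50%.** SE of the gap = √(p_d(1 − p_d)/30 + p_m(1 − p_m)/15).
- Mania 67%: accuracy 50% v 67%, gap 17 points. SE = √(0.25/30 + 0.2211/15) = 0.152, so the gap is about 1.1 SE.
- Mania 80%: accuracy 50% v 80%, gap 30 points. SE = √(0.25/30 + 0.16/15) = 0.138, so the gap is about 2.2 SE.

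**Model with some skill, equal in both groups.** Take sensitivity 0.85 and specificity 0.60, with response 40% v 70%.
- Depression: 0.85 × 0.40 + 0.60 × 0.60 = 0.700.
- Mania: 0.85 × 0.70 + 0.60 × 0.30 = 0.775.
- The gap is 7.5 points, while balanced accuracy is (0.85 + 0.60)/2 = 0.725 in both.

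**How often a no-skill rule would give nominal two-sided p < 0.05.** The rule always predicts the pooled majority class. The figures come from exact binomial enumeration of the pooled z-test. The 15 v 8 column stands for about half the sample being held out.

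| Response, depression v mania | Accuracy, depression v mania | Chance at 30 v 15 | Chance at 15 v 8 |
|---|---|---|---|
| 60% v 60% | 60% v 60% | 0.05 | 0.05 |
| 50% v 70% | 50% v 70% | 0.23 | 0.13 |
| 40% v 60% | 60% v 40% | 0.24 | 0.15 |
| 50% v 80% | 50% v 80% | 0.50 | 0.27 |
| 30% v 70% | 70% v 30% | 0.73 | 0.46 |

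**When no gap appears.**
- A coin flip (q = 0.5) gives a gap of exactly zero at any rates.
- A majority rule fitted within each polarity gives none when the rates mirror each other around 50% (40% v 60% gives 60% in both).
- A model with sensitivity equal to specificity (0.80 and 0.80) gives none.

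**Polarity as a proxy in pooled results.** Suppose a score does nothing but separate manic from depressed patients. Its pooled AUC for response is 0.5 + 0.5 × [P(manic | responder) − P(manic | non-responder)]. With depression at 50% this is 0.577, 0.614 or 0.639 for mania at 67%, 75% or 80%. At 80%, for example: 0.5 + 0.5 × (12/27 − 3/18) = 0.639. The features planned in section 2.6 include the mean and variance of activity, which could carry this information.

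**The case against.** The strongest defence is that the article does not fix percent correct. Accuracy sits beside the broader word performance, Research Question 3 itself asks only whether polarity is a moderator, and the article cites AUC when it describes an earlier prospective study. Study-level detail is deferred to a Study 3 protocol and an analysis plan, and the project calls itself exploratory. This has weight: the word may be loose. But the sentence describing the analysis names accuracy on a binary outcome as the quantity to be compared, and a named measure can be improved now.

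Four stronger readings are tempting, and the document does not support them.
- A reader might infer that a no-skill model would necessarily show moderation. It can, but the gap vanishes for a coin flip and is only about 1.1 SE in the low case above.
- A reader might infer that the plan states that 8-week response rates differ. The statement in section 2.6 concerns probability of recovery, gives no rates, and is used to argue for joint modelling of episode types. The step to Study 3 response is an inference, supported by section 1.4.
- The use of different rating scales might seem to force different rates. A 50% relative reduction on two scales does not imply that.
- A reader might conclude that Research Question 2 performance is inflated. The article names no metric there and does not say that results will be pooled over polarity.

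**Conclusion.** The concern holds in a limited form. As worded, the analysis compares a quantity that can differ between polarities through response rates alone, and the article gives reason to expect those rates to differ. Under the assumed rates of 50% in depression and 67% to 80% in mania, the gap for an always-predict-response rule is 17 to 30 points. Across the unequal-rate scenarios tabulated, a no-skill majority rule reaches nominal significance with probability 0.23 to 0.73 at 30 v 15, and less often if part of the sample goes to training.

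The conclusion rests on two things: that accuracy means percent correct, and that response rates do differ by polarity. Because this is a secondary, exploratory aim, the consequence is a possible misreading of one result. The proxy issue for Research Question 2 is a precaution about reporting, since that analysis is not specified.

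**What to change.** In section 2.2, and in the Study 3 protocol or analysis plan, replace model accuracy with a measure that does not depend on the response rate, computed within each polarity. Any of these would serve:
- AUC;
- sensitivity and specificity, or balanced accuracy;
- skill relative to that polarity's own no-information rate.

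Report the difference between polarities with a confidence interval, as an exploratory estimate. For Research Question 2, report Study 3 performance within each polarity alongside any pooled figure.

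The change costs only wording, but it exposes how little the sample can say. As an illustration, assume an AUC of 0.70 in both groups and response of 80% in mania (12 responders, 3 non-responders) and 50% in depression (15 and 15). The Hanley-McNeil standard errors are about 0.16 and 0.10. The 95% interval for the difference then has a half-width of about 0.37, before any patients are moved to training. The text should say so.

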## Protocol

2.

To ensure clarity and appropriate detail for a project with this hierarchical structure, a multi-paper registration strategy has been adopted. Study-specific methodological details essential for direct replication of each component (e.g., detailed assessment schedules, site-specific recruitment procedures, and embedded sub-studies) will be provided in three forthcoming, cross-referenced study-level protocols [
2]. This manuscript presents the overarching project protocol, detailing the scientific rationale, the high-level design of the three empirical studies, and the cross-study analytic plan (WP4).
Box 1 provides an overview and comparison of the three studies’ methods.

Box 1. Comparison of methods across three empirical work packages.**Table T1:** 

Design Feature	Study 1 (Australia)	Study 2 (India)	Study 3 (New Zealand)
Primary Aim	Develop and train a predictive model for relapse risk from RAR data.	Replicate the relapse model in a low-middle income context and test biological correlates of RAR.	Test generalisability of the relapse model to predict treatment response (recovery).
Population	Adults with interepisode BD I or II.	Adults with interepisode BD I or II, plus matched healthy controls.	Adults experiencing an acute manic or depressive episode of BD I or II.
Setting	Outpatients/Community recruitment.	Outpatients/recruitment via hospital-based clinicians.	Predominantly inpatients, some outpatient recruitment via clinicians.
Primary Predictor	Actigraphy (RAR variables) over 14 days (at baseline of three epochs).	Actigraphy (RAR variables) over 14 days (at baseline of one epoch).	Actigraphy (RAR variables) over 14 days (at baseline).
Primary Outcome	Time to Relapse over three 26-week epochs (measured via retrospective LIFE interview on two occasions per epoch).	Time to Relapse over a 26-week epoch (measured via retrospective LIFE interview on two occasions over 26 weeks).	Treatment Response (≥50% symptom reduction) at 8 weeks.
Biological Sampling	No	Yes (blood samples) for circadian gene expression and metabolomics.	No
Clinical Predictors in models	Yes (five key clinical variables included as covariates, e.g., BD subtype, residual symptoms).	Yes (five clinical variables included to enable direct replication of Study 1).	No (to minimise participant burden in an acutely ill population).

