**Figure 1. f1:**
[figure not shown]
Study 1 design overview.

The three analytic approaches generate distinct, complementary research questions for the project’s primary aim of algorithm development:
•Research Question 1: Do Relative Amplitude, Intradaily Variability, and/or Interdaily Stability emerge as independent predictors of time to relapse using Cox Survival Analysis?•Research Question 2: Can a Dynamic Bayesian Network Analysis of RAR parameters predict change in BD psychopathology and full-threshold relapses in a sample of individuals with BD I and II?•Research Question 3: Can Hadaeghi’s Complex System Model, trained on statistical, time-frequency, and nonlinear dynamic features from RAR data collected from a cohort of
*n* = 75 participants predict relapse in an unseen subset of
*n* = 25 participants?•Research Question 4: Do the three approaches to analysis (Cox Survival Analysis, Dynamic Bayesian Network Analysis, and Hadaeghi’s Complex System Model) generate convergent findings about relapse risk prediction from RAR?

*Study 2: Exploring replicability of models in a lower-middle income sample; testing molecular rhythmicity correlates of RAR variables.*

Study 2 (India) repeats Study 1’s prospective design amongst interepisode individuals with BD, but with only one 26-week epoch (
Figure 2). Study 2 aims, first, to explore the replicability of Study 1’s models of relapse prediction in an out-of-distribution cohort from a lower-middle income country (LMIC). Secondly, Study 2 will, (i) test the mechanistic prediction that Relative Amplitude will correlate with diurnal amplitudes of gene expression and metabolites in blood, and (ii) test the hypothesis that both Relative Amplitude and diurnal amplitudes of gene expression and metabolites in blood are attenuated in individuals with BD (
*N* = 25) relative to matched healthy controls (
*N* = 25).

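### Study 3 aims to test whether the relapse model generalises to treatment response, but its research questions evaluate a model retrained on Study 3 patients, and none explicitly tests the unretrained model

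*Protocol article*

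**What the plan says.** Box 1 gives the primary aim of Study 3 as: "Test generalisability of the relapse model to predict treatment response (recovery"). Section 2.2 (Study 3) repeats it: the question is whether the algorithm "trained and tested on Study 1 data) can be extended to response to treatment". It also says what success would suggest, namely that the complex system model "captures generic system instability (as opposed to a relapse-specific process"). That reading is introduced cautiously: "If generalisation is demonstrated, it could be hypothesised that".

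The research questions later in the same section are worded differently.
- **Research Question 1** asks how many samples (x) from the "Study 3 sample are required to retrain the Study 1 complex system model predicting relapse", "to achieve acceptable prediction accuracy for" a state transition model covering both relapse and response.
- **Research Question 2** trains on 75 Study 1 samples plus x Study 3 samples and tests on a single set described as unseen, in the words "from Research Question 1) Study 3 samples predict state transition in an unseen data set of": 25 from Study 1 and 45 − x from Study 3.

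Study 1's Research Question 3 already uses a split of the same size: a model trained on "75 participants predict relapse in an unseen subset of" 25.

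**The concern.** A model that has been shown x labelled Study 3 responders and non-responders can learn treatment response directly from them. If it then predicts response in other Study 3 patients, the relapse-trained part may have contributed much, little or nothing. The result would not separate these cases, yet the generic-instability reading depends on separating them. That reading carries the second part of the project's secondary aim (Introduction).

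Two further points follow from the text as risks, not as stated rules. First, x has to be judged against some accuracy criterion, and the two splits name no separate data for that. Second, the test set joins an interepisode cohort labelled for relapse with an acutely ill cohort labelled for 8-week response. If performance is computed over the joined set, a model can score well by telling the cohorts apart.

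**Working it through.** **1. Aim against test.** The aim concerns a model trained and tested on Study 1. Research Question 2 evaluates a model trained on 75 + x. The two coincide only at x = 0, which no question specifies. By contrast, Study 2's Research Question 3 does ask whether the model derived in Study 1 replicates in a new cohort.

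**2. Accounting for the data.** 75 + 25 = 100 uses all of Study 1, and x + (45 − x) = 45 uses all of Study 3. No third subset is named for choosing x. It could still be chosen by cross-validation inside the 75 + x.

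**3. Base rates.** The plan's own figure reproduces: 100 participants × 1.5 years × 0.4 episodes per year = 60 relapses (Discussion). At a constant rate, the probability of relapse per participant is:
- 26 weeks: 1 − exp(−0.2) = 0.18
- 78 weeks: 1 − exp(−0.6) = 0.45

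The protocol gives no Study 3 response rate, so 50% to 70% is assumed.

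**4. Cohort-only AUC if the combined set is scored as one.** Take a score that knows only the cohort and has no skill within it. Then AUC = 0.5 + [P(Study 3 | event) − P(Study 3 | no event)] / 2. Use 25 + 25 test patients (x = 20), one label each, with the cohorts perfectly distinguishable.

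| Study 1 relapse | Study 3 response (assumed) | P(Study 3 given event) | P(Study 3 given no event) | AUC |
|---|---|---|---|---|
| 18% | 50% | 12.5/17.0 = 0.735 | 12.5/33.0 = 0.379 | 0.68 |
| 18% | 60% | 15/19.5 = 0.769 | 10/30.5 = 0.328 | 0.72 |
| 45% | 50% | 12.5/23.75 = 0.526 | 12.5/26.25 = 0.476 | 0.525 |
| 45% | 60% | 15/26.25 = 0.571 | 10/23.75 = 0.421 | 0.575 |
| 45% | 70% | 17.5/28.75 = 0.609 | 7.5/21.25 = 0.353 | 0.63 |

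So the effect is material with per-epoch labels and can be close to nothing with 78-week labels. Section 2.6 says that outcomes will label actigraphy epochs, which leans towards the per-epoch case but does not settle it.

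**5. Choosing x on the left-over patients.** This is a simulation with no Study 3 signal. Assumptions: AUC of 0.70 or more counts as acceptable, x moves in steps of 5, response is 50–60%, and predictions at different x are correlated 0 to 0.9. Each row gives the probability that the no-skill model looks acceptable.

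| Largest x | Searching from x = 5 up to it | One look at that x |
|---|---|---|
| 15 | 5–8% | 3–4% |
| 25 | 11–19% | 7–8% |
| 30 | 17–29% | 11–12% |
| 35 | 26–42% | 17–20% |

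A single look at x = 5 gives about 1–2%. Much of the rise down the table therefore comes from the shrinking test set. The search itself adds a factor of roughly 1.4 to 2.6.

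**6. Precision of a frozen-model test.** Hanley–McNeil: SE² = [A(1 − A) + (n₁ − 1)(a − A²) + (n₀ − 1)(b − A²)] / (n₁n₀), with a = A/(2 − A) and b = 2A²/(1 + A). At A = 0.70, a = 0.5385 and b = 0.5765. With all 45 and 50% response (n₁ = n₀ = 22.5): SE² = (0.21 + 21.5 × 0.0485 + 21.5 × 0.0865)/506.25 = 0.00614. So SE = 0.078 and the 95% half-width is 0.15. With 30 patients (x = 15) it is 0.19, and with 20 (x = 25) it is 0.23.

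**The case against.** The strongest defence is that Research Question 1 is a learning-curve question. Zero is a possible answer and would amount to direct transfer. A small x would be some evidence of shared structure. The section describes its questions as developing and testing a state transition model, the inference is hedged, and the project calls itself exploratory and says replication elsewhere is essential. This stands against any claim that the design cannot show generalisation. It does not remove the mismatch: unless the unretrained accuracy happens to be judged acceptable, the text plans no transfer result.

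A reader might infer that x will be picked on the very patients called unseen. The documents do not say so. Research Question 1 names no evaluation data, cross-validation inside the training data is possible, and section 2.6 leaves detail to a later analysis plan. Likewise, the 25 Study 1 patients may be the hold-out already scored in Study 1, but this is not stated.

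A reader might also infer that one pooled accuracy will be reported. Research Question 2 names a combined test set but no pooled metric, and Study 3's secondary aim looks at accuracy by episode polarity, which is evaluation within Study 3. Both points therefore remain risks to close off, not errors in the plan.

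**Conclusion.** The point holds as a mismatch between aim and test. Study 3 sets out to test whether the relapse model generalises, and its research questions evaluate a retrained joint model without explicitly testing the unretrained one. A positive answer could credit transfer with what was learned directly from Study 3 labels. This follows from the text and needs no assumption.

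The sizes of the two further risks are conditional. The cohort-only AUC depends on the labelling window, the assumed response rate and perfect separation of the cohorts. The inflation from choosing x depends on an assumed threshold and grid, and on x being searched on the left-over patients at all. None of these figures predicts what the study will report.

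This should be fixed, because it concerns Study 3's primary aim. It is not a fatal flaw: the aim is a mechanistic, exploratory one at project level, and the remedy touches only the analysis.

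**What to change.** - **Generalisability test.** Apply the frozen Study 1 model (x = 0) unchanged to all 45 Study 3 participants and report the AUC with its confidence interval.
- **Retraining.** Keep it as a secondary learning curve. Fix x in advance, or choose it only by cross-validation inside the training data. At each x, compare with a model trained on the same x Study 3 cases alone, and credit to transfer only the gain over that model.
- **Reporting.** Give performance separately for the Study 1 and Study 3 test patients. State whether the 25 are the Study 1 hold-out and, if so, that they have already been scored.

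Recruitment, visits and measures do not change. The cost is wording in the Study 3 protocol or analysis plan and extra computing. The downside is a probably less favourable and imprecise headline figure, although the frozen test uses more Study 3 patients than any retrained version can.
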